### Data Analysis

Preoperative outcomes assessed at T1 (preoperative state anxiety and preoperative pain) will be analyzed using ANCOVA with the treatment group as the between-subject factor (NADA vs CTRL) and the respective baseline value as the covariate. Adjusted mean differences between groups and effect sizes (Cohen *d*) will be reported with corresponding 95% CIs. A 2-sided significance level of 5% will be applied.

In an exploratory analysis, the time interval between the T1 STAI-S assessment and surgery will be included as an additional covariate to account for potential variability in the timing of the anxiety assessment. Some variation in timing is expected due to the practical constraints of conducting the study in a clinical setting, and preoperative anxiety may increase as surgery approaches.

Repeated continuous postoperative outcomes T2-Tx (state anxiety, pain, PONV) will be analyzed using linear mixed-effects models including fixed effects for treatment group, time, and the group × time interaction, with participants included as a random effect.

Cumulative analgesic and antiemetic medication use from surgery to discharge will be compared between groups using linear regression models. If substantial violations of model assumptions are observed that cannot be addressed through appropriate data transformations, alternative analyses will be used, such as generalized linear models. Overall postoperative complication rates will be analyzed using logistic regression models and reported as odds ratios (ORs) with corresponding CIs.

Exploratory moderation analyses will be performed to evaluate whether baseline characteristics, including surgery-specific preoperative anxiety, trait anxiety, and depressive symptoms, modify the treatment effect on the primary outcome. Separate models will be fitted for each moderator as extensions of the primary ANCOVA model. Each model will include the baseline covariate, the treatment group, the respective moderator, and the group x moderator interaction term. A significant interaction term will be interpreted as evidence of a moderating effect.

All analyses will be conducted according to the intention-to-treat (ITT) principle. All randomized participants will be included in the analysis and analyzed according to their allocated group, irrespective of adherence to the intervention. Missing data will be handled using multiple imputation by chained equations (MICE) under the assumption that data are missing at random using the “mice” package for R [46]. Due to the nature of longitudinal data collection, between-participant variation in number of hospitalization days is expected and will be accounted for. Observations expected during hospitalization but not available will be imputed; however, measurements not collected because of hospital discharge will not be imputed. Analyses will be performed on multiply imputed datasets, and parameter estimates across the imputed datasets will be combined using Rubin’s rule.

As a sensitivity analysis, a per-protocol analysis will be conducted, including only participants who adhered to their allocated treatment. Protocol adherence will be defined a priori. Participants in the intervention group will be considered protocol-adherent if they received the ear acupressure prior to surgery and continued the intervention for the subsequent 4 days or until hospital discharge, whichever occurred first. Participants in the control group will be considered adherent if they did not receive ear acupressure before the end of primary data collection (Tx).

In addition, an exploratory exposure-based sensitivity analysis will be performed at 3 months follow-up to assess the association between exposure to ear acupressure and the use of other CIM therapies. To this end, participants will be classified according to actual exposure to ear acupressure, defined as receipt of ear acupressure either during the intervention phase or after discharge in the control group. ORs and corresponding 95% CIs will be calculated to compare the likelihood of using CIM therapies between participants exposed to ear acupressure and those not exposed.

No formal adjustment for multiplicity will be applied, as the trial has a single primary outcome for the confirmatory analysis. Findings for the secondary outcomes, as well as the moderation and sensitivity analyses, are considered subsidiary and exploratory [47].

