### Randomization and Blinding

Participants (N=66) will be enrolled and randomly assigned in a 1:1 ratio to either the intervention group (NADA) or the control group (CTRL). The random allocation sequence will be generated by an independent statistician who is not involved in participant recruitment, enrollment, or intervention delivery. The sequence will be created using the R (R Foundation for Statistical Computing) package “blockrand” [37] and implemented via the REDCap (Research Electronic Data Capture; Vanderbilt University) [38]. Restricted randomization with blocks of variable lengths will be used to ensure balanced group sizes throughout the recruitment period and reduce predictability of group assignment. Stratified randomization will be performed according to the type of breast surgery, with 2 predefined strata: breast-conserving therapy and mastectomy.

Allocation concealment will be ensured through centralized randomization within REDCap. The allocation sequence will be integrated in the secure electronic system and will not be accessible to investigators responsible for screening or enrolling participants.

Participants will be enrolled by the study physician. Randomization will be performed electronically in REDCap after completion of baseline data collection. The group assignment will be revealed only after a participant has been enrolled and a baseline assessment (T0) has been completed. Study personnel responsible for enrollment and allocation will not have access to the full randomization list or information regarding block sizes.

Due to the nature of the auricular acupressure intervention, blinding of participants and study personnel is not feasible. However, statistical analyses will be performed by statisticians who are blinded to group allocation.

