## Discussion

The present trial aims to evaluate the effectiveness of auricular acupressure according to the NADA protocol in addition to standard preoperative care in reducing perioperative anxiety and pain in women with a first diagnosis of breast cancer undergoing therapeutic surgery. It is hypothesized that auricular acupressure will be superior to standard care in reducing perioperative anxiety and pain in this patient population. This hypothesis is in line with previous findings, including both emergency and elective surgeries in clinically heterogeneous populations [15], and initial evidence suggesting beneficial effects of the NADA protocol in oncological patients outside the surgical context [24-26].

This trial has several methodological strengths. To the best of our knowledge, this is the first randomized controlled trial to evaluate NADA auricular acupressure in the perioperative context of breast cancer surgery. By focusing on a standardized 5-point auricular protocol applied within a defined perioperative time frame, this study seeks to address the substantial variability in acupuncture techniques, point selection, and treatment duration from previous research. Furthermore, the use of this standardized protocol enhances reproducibility and may facilitate future implementation in routine clinical care if efficacy is demonstrated. The randomized controlled design with centralized allocation concealment reduces the risk of selection bias. Stratified randomization according to surgical procedure further minimizes potential confounding. Another strength of this trial is that it is conducted within a real-world perioperative oncology setting and embedded into routine clinical care. The intervention is delivered under pragmatic conditions, which enhances the external validity of the findings.

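### Randomisation is stratified by surgery type, but the primary ANCOVA and the other linear models with listed terms leave that factor out; if it is prognostic, the test is conservative and some precision is forgone

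*Protocol article*

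**What the plan says.** Under Randomization and Blinding: "Stratified randomization will be performed according to the type of breast surgery, with 2 predefined strata: breast-conserving therapy and mastectomy". The same section adds permuted blocks: "Restricted randomization with blocks of variable lengths will be used to ensure balanced group sizes". The Discussion counts this as a strength: "Stratified randomization according to surgical procedure further minimizes potential confounding".

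Under Data Analysis, three models have their terms listed, and none contains surgery type:

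- T1 state anxiety (primary) and T1 pain: "will be analyzed using ANCOVA with the treatment group as the between-subject factor (NADA vs CTRL) and the respective baseline value as the covariate".
- Anxiety, pain and PONV from T2 onwards: "linear mixed-effects models including fixed effects for treatment group, time, and the group × time interaction, with participants included as a random effect".
- Moderation models, built as extensions of the primary ANCOVA: "Each model will include the baseline covariate, the treatment group, the respective moderator, and the group x moderator interaction term".

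Two further models are named without any covariate list:

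- Medication: "Cumulative analgesic and antiemetic medication use from surgery to discharge will be compared between groups using linear regression models".
- Complications: "Overall postoperative complication rates will be analyzed using logistic regression models and reported as odds ratios (ORs) with corresponding CIs".

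The Sample Size Calculation uses the same two-term ANCOVA (group and baseline STAI-S). The exploratory timing analysis and the per-protocol analysis do not bring surgery type in either, and no reason for leaving it out is given.

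**The concern.** Blocking within strata forces the arms to be nearly balanced on surgery type. Any outcome difference between the two operations therefore hardly contributes to the true sampling error of the treatment comparison. A linear model without the stratum still leaves that difference in its residual variance, so the standard error it reports exceeds the true one. Confidence intervals are then wider than they need be, the actual type I error falls below 5%, and the benefit for which the trial stratified is only partly collected.

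The article gives qualitative reasons why surgery type could matter. The Introduction links changes in body image to anxiety. The Participants section gives stays of 1 to 3 days for breast-conserving surgery and 3 to 5 days for mastectomy, while medication is totalled from surgery to discharge. Because measurements after discharge are not imputed, the later days in the mixed models will probably come increasingly from mastectomy patients.

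**Working it through.** **1. The plan's own figure.** Inputs from the Sample Size Calculation: difference 8, SD 10, so d = 0.8 and f = 0.4; two-sided alpha 0.05; power 80%; ANCOVA with one covariate. Using the noncentral F with 1 and N − 3 degrees of freedom and noncentrality f²N, power is 0.799 at N = 51 and 0.807 at N = 52. The stated 52 reproduces. With 20% dropout, 52/0.8 = 65, and 66 is the next even number.

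**2. Cost of adding the stratum if it is not prognostic.** With N − 4 denominator degrees of freedom, power at N = 52 is still 0.807 and the required N is still 52.

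**3. Standard-error inflation from leaving it out.** Assumptions, none in the documents: proportion of mastectomies p = 0.30; total residual SD 10 after baseline (as in the plan's calculation, which keeps f = 0.4 and credits nothing to the baseline correlation); residual gap g between strata in T1 STAI-S. The share of residual variance due to surgery type is R² = g²p(1 − p)/100, and the ratio of reported to true standard error is about 1/√(1 − R²) under near-perfect balance.

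| g (points) | R² | SE ratio |
|---|---|---|
| 0 | 0 | 1.000 |
| 2 | 4 × 0.21/100 = 0.0084 | 1.004 |
| 4 | 16 × 0.21/100 = 0.0336 | 1.017 |
| 6 | 36 × 0.21/100 = 0.0756 | 1.040 |
| 8 | 64 × 0.21/100 = 0.1344 | 1.075 |

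**4. Type I error and power.** Simulation with stratified permuted blocks (sizes 2, 4 and 6 assumed), N = 52, 6,000 trials per scenario, both models fitted to the same data:

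| g | Type I, without stratum | Type I, with stratum | Power, without | Power, with |
|---|---|---|---|---|
| 0 | 0.050 | 0.050 | 0.802 | 0.799 |
| 2 | 0.053 | 0.054 | 0.790 | 0.795 |
| 4 | 0.046 | 0.051 | 0.803 | 0.814 |
| 6 | 0.044 | 0.050 | 0.804 | 0.823 |
| 8 | 0.038 | 0.052 | 0.813 | 0.846 |

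Monte Carlo error is √(0.05 × 0.95/6000) ≈ 0.003 for type I error and √(0.8 × 0.2/6000) ≈ 0.005 for power. The type I figure at 4 points is therefore not clearly separated from 5% by simulation alone. Theory gives the same size: multiplying the critical value 1.96 by the SE ratios for 4, 6 and 8 points gives two-sided tail areas of about 0.046, 0.041 and 0.035. With all 66 patients and an 8-point gap, power is 0.902 without and 0.926 with the stratum.

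Power without the stratum stays near 80% at N = 52 throughout, because an SD of 10 already contains any variance between strata.

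**5. Medication totals (illustration).** Assume equal daily use, mid-range stays of 2 and 4 days, 35% mastectomy and a within-stratum SD of 2 to 3 day-doses. The between-stratum variance is 2² × 0.35 × 0.65 = 0.91. A model without the stratum inflates the standard error by √(1 + 0.91/9) = 1.05 to √(1 + 0.91/4) = 1.11.

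**6. Complications (illustration).** Assume 66 patients, 30% mastectomy, a 10% control risk in the breast-conserving stratum, treatment odds ratio 0.5 and stratum odds ratio 4. The standard error of the log odds ratio is 0.767 without and 0.789 with the stratum. The log odds ratio is −0.656 without and −0.693 with it. Here omission shrinks the odds ratio towards 1; it does not widen the standard error.

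**The case against.** The strongest reply is that the error is on the safe side and small. It cannot create a false positive, the plan keeps its 80% power, and the loss exists only relative to a better model. That stands.

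It can also be said that the loss may be nil. The primary outcome is measured before the operation, so surgery type can act only through anticipation or through differences between patients. The stratum is needed for randomisation straight after T0, so the planned operation is probably known around T0, and baseline STAI-S may absorb much of the gap. An 8-point gap equals the trial's own minimal important difference and is a generous upper end. This stands too, and it is why the point must be conditional.

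The reply that a condensed article leaves such detail to the analysis plan holds only in part. It covers the medication and complication regressions, whose covariates are not listed, so silence there does not establish omission. It does not cover the ANCOVA, the mixed models and the moderation models, whose terms are spelled out; the sample-size model repeats the two-term ANCOVA.

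A reader might infer more: that the trial is underpowered, that the estimate is biased by surgery type, or that every planned model reports too large a standard error. The documents support none of these. The power calculation reproduces and holds without the stratum, stratified allocation itself protects against confounding by surgery type, and the standard-error mechanism does not carry over to the logistic model.

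**Conclusion.** The mismatch between design and analysis is real and stated in the text: stratified allocation, but no stratum in the primary ANCOVA, the mixed models or the moderation models. The consequence is conditional and modest. For residual gaps of 4 to 8 STAI-S points with 30% mastectomy and residual SD 10, the reported standard error is about 2 to 7.5% too large, type I error is about 4.6 to 3.8%, and about 1 to 3 points of power are forgone. At 2 points the effect is negligible, and at zero there is none. The documents give no figure that places the trial within this range. The planned 80% power at 52 is not undermined, so this is an inexpensive improvement that should be made, not a defect that threatens the confirmatory conclusion. For medication totals the case for the stratum is plausible because length of stay differs by operation, but those analyses are exploratory.

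**What to change.** State in the analysis section or the analysis plan that the stratum used at randomisation (breast-conserving therapy versus mastectomy) enters the primary ANCOVA as a fixed effect. Do the same for T1 pain, the T2–Tx mixed models, the moderation models and the medication regressions. For the complication model, make adjustment depend on the number of events, since 66 patients may yield few in-hospital complications, and say whether the reported odds ratio is conditional on the stratum or marginal.

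The cost is one or two sentences and one degree of freedom per model. No new data are needed and the sample size stays at 52 evaluable and 66 enrolled. Only 8 participants had been recruited at submission, so the term can still be fixed before any outcome comparison; added later it would look data-driven.

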### Sample Size Calculation

As this is, to the best of our knowledge, the first study investigating the effects of ear acupressure on preoperative anxiety, we opted for a clinically meaningful effect to be the most appropriate basis for the sample size calculation [31,32]. The sample size was determined to ensure adequate statistical power to detect a clinically important difference between groups on the (STAI-S) [33]. Based on an 8-point minimal clinically important difference [34] and assuming an SD of 10 based on previous data in similar populations [35], this amounts to a large effect size (Cohen *d*=0.8; *f*=0.4).

The sample size estimation was performed using G*Power (version 3.1, Heinrich Heine University Düsseldorf, Germany) [36] specifying a covariance analysis (ANCOVA) with the treatment group as the between-subject factor and the baseline STAI-S score as a covariate, a 2-sided significance level of 5%, and a statistical power of 80%. This yielded a required total sample size of 52 patients. To account for an anticipated dropout rate of 20%, a total of 66 participants will be enrolled in the study.

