**Figure 1. F1:**
[figure not shown]
SPIRIT (Standard Protocol Items: Recommendations for Interventional Trials) 2025 participant timeline: schedule of enrollment, interventions, and assessments. NADA: The National Acupuncture Detoxification Association.

The primary outcome of this study is preoperative state anxiety prior to surgery (T1) measured using the State subscale of STAI-S [33].

Secondary outcomes include postoperative anxiety, preoperative and postoperative pain, PONV, use of analgesic and antiemetic medication, postoperative complications, specific surgery-related preoperative anxiety, trait anxiety, depressive symptoms, and therapy decisions at follow-up.

Postoperative anxiety will be measured using STAI-S after transfer to the surgical ward (T2) and daily during hospitalization (T3-Tx). Current pain intensity will be assessed using a Numerical Rating Scale (NRS; 0‐10) where higher scores represent higher pain intensity and will be measured both pre- (T0 and T1) and postoperative (T2-Tx). PONV will be assessed jointly using an NRS (0‐10) where higher scores represent higher symptom severity. Assessments will be performed after transfer to the surgical ward (T2) and daily during hospitalization (T3-Tx). This approach is consistent with current perioperative research and clinical practice, as nausea and vomiting are considered to share common risk factors and are addressed together in current clinical guidelines for the prevention and management of PONV [40,41]. For outcomes assessed daily during hospitalization, the same standardized questions were used at each assessment timepoint to ensure consistency across repeated measurements.

Analgesic consumption and the use of antiemetic medication will be extracted from medical records and summarized from surgery until discharge. Due to possible variability in prescribed agents and dose adjustments based on symptom severity, medication use will be summarized by drug class (eg, opioids, nonopioid analgesics, and antiemetics). Opioid consumption will be converted to oral morphine equivalents (OME) to allow standardized comparisons across participants [42]. Nonopioid analgesics and antiemetics will be summarized as cumulative dose within class and frequency of administration (eg, number of doses given).

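### The postoperative mixed models for state anxiety and pain leave out the pre-randomization T0 score, which costs precision in two exploratory analyses

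*Protocol article*

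**What the plan says.** All references are to the protocol article.

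- **Data Analysis, T1 outcomes.** Preoperative state anxiety and pain are analyzed by ANCOVA with "treatment group as the between-subject factor (NADA vs CTRL) and the respective baseline value as the covariate". The exploratory moderation models, which extend the primary ANCOVA, also name the baseline covariate.
- **Data Analysis, T2 to Tx outcomes.** The article states: "Repeated continuous postoperative outcomes T2-Tx (state anxiety, pain, PONV) will be analyzed using linear mixed-effects models including fixed effects for treatment group, time" and the interaction of the two, with a random effect for participant. No baseline term is listed, and T0 is not one of the modelled time points.
- **Sample Size Calculation.** The primary ANCOVA is specified with "the treatment group as the between-subject factor and the baseline STAI-S score as a covariate".
- **Outcomes.** Pain intensity "will be measured both pre- (T0 and T1) and postoperative (T2-Tx"). For PONV, "Assessments will be performed after transfer to the surgical ward (T2) and daily during hospitalization (T3-Tx"), so it has no T0 value.
- **Randomization and Blinding.** "Randomization will be performed electronically in REDCap after completion of baseline data collection".

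The article nowhere else adds baseline adjustment to the postoperative models. The end of Data Analysis classes the secondary outcomes as exploratory.

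**The concern.** One section handles the same two scales in two ways. At T1 the STAI-S and pain scores are adjusted for their T0 values; after surgery they are not. The T0 scores precede allocation, so they are valid covariates and should exist for essentially every randomized patient.

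The participant random effect does not do the same job. It describes how one person's postoperative scores hang together. It does not use T0 to explain differences between people, and it does not remove a T0 difference between the arms.

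Precision is what is at stake. The stated objective covers perioperative anxiety and pain, so the postoperative period belongs to the question. The Discussion concedes that the trial is not powered for secondary outcomes and relies on estimates with confidence intervals to show magnitude and precision. With about 33 patients per arm, intervals that are wider than they need to be weaken that plan.

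**Working it through.** **Inputs from the article.** Difference 8 points, SD 10, d = 0.8, f = 0.4; two-sided 5% level; 80% power; N = 52 before dropout; 20% dropout; 66 enrolled 1:1, so 33 per arm.

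**Assumed inputs.** The article gives no correlation r between T0 and postoperative scores, so r is varied from 0.3 to 0.7. The correlation between a person's postoperative scores is set at 0.6. SDs are taken as equal at all time points. The formulas ignore the small cost of estimating the slope.

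**Step 1: the plan's own figure.** For an ANCOVA with two groups and one covariate (numerator df 1, denominator df N − 3, noncentrality f²N), power is 0.799 at N = 51 and 0.807 at N = 52. The stated 52 is reproduced. 52/0.8 = 65, and 66 is the next even number. The primary calculation stands.

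**Step 2: one postoperative visit, STAI-S.** Unadjusted SE = 10·√(2/33) = 2.46. Adjusted SE = 2.46·√(1 − r²). The equivalent gain in patients is 1/(1 − r²) − 1. Power is for an illustrative 5-point difference.

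| r | Variance removed | SE | 95% CI half-width | Equivalent extra patients | Power, 5 points |
|---|---|---|---|---|---|
| no T0 | – | 2.46 | 4.83 | – | 53% |
| 0.3 | 9% | 2.35 | 4.60 | 10% | 57% |
| 0.5 | 25% | 2.13 | 4.18 | 33% | 65% |
| 0.6 | 36% | 1.97 | 3.86 | 56% | 72% |

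**Step 3: mean of k postoperative visits.** In units of SD², the unadjusted variance is v = (1 + (k − 1)·0.6)/k and the adjusted variance is v − r².

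- k = 2: v = 0.80. At r = 0.3 it falls to 0.71 (0.80/0.71 = 1.13, or 13% more patients). At r = 0.5 it falls to 0.55 (ratio 1.45, or 45% more).
- k = 3: v = 0.733. At r = 0.3 it falls to 0.643 (ratio 1.14, or 14% more). At r = 0.5 it falls to 0.483 (ratio 1.52, or 52% more).

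**Step 4: chance imbalance at T0.** The T0 difference between arms has SD 2.46 points. A difference of 4 points or more in either direction has probability 2·(1 − Φ(4/2.46)), about 10%. It moves the unadjusted postoperative estimate by about 4r: 1.2 points at r = 0.3, 2.0 at r = 0.5 and 2.8 at r = 0.7.

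**Step 5: simulation check.** 66 participants, three visits, 150 replicates per setting.

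| r | Correlation between visits | Empirical SD of group effect, no T0 | With T0 |
|---|---|---|---|
| 0.3 | 0.6 | 1.99 | 2.01 |
| 0.5 | 0.6 | 2.21 | 1.74 |
| 0.6 | 0.7 | 2.06 | 1.61 |

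At r = 0.3 the expected gain (SE 2.11 to 1.97 by the Step 3 formula) is lost in simulation noise. At r = 0.5 and 0.6 the unadjusted estimate followed the T0 difference with slopes of 0.48 and 0.52; the adjusted slopes were −0.02 and −0.07.

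**The case against.** **The article is condensed, and its wording for the mixed models could be non-exhaustive.** Covariate lists for secondary models are often left to an analysis plan. That carries limited weight here, because the same section names the baseline covariate where it is used, for the T1 outcomes and for the moderation models. If adjustment is intended, the same line is needed to say so.

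**The analyses are exploratory and the gain rests on an assumed r.** Both points stand. At r = 0.3 the gain is modest. Nothing in the article shows how well preoperative pain predicts pain after breast surgery, so the STAI-S figures should not be carried over to pain without caution.

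**Stronger readings that the documents do not support.**

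- A reader might infer that the unadjusted models are biased or give invalid intervals. They do not: under randomization the contrast is unbiased, and its standard error already includes chance baseline variation. Lost precision and carried imbalance are therefore largely one cost, not two.
- A reader might infer that a T0 imbalance enters the postoperative contrast in full and is likely to be large. It enters scaled by the slope, and a difference of 4 points or more has only about a 10% chance.
- A reader might infer that the T1 and postoperative effects measure different things. In a linear model the adjusted and unadjusted contrasts target the same mean difference; only their precision differs.

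**Conclusion.** The point holds as an avoidable loss of efficiency in two exploratory analyses. It is not an error of validity, and the primary ANCOVA and the sample size of 52, or 66 with dropout, are unaffected.

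For STAI-S at a single visit, the gain runs from 10% to 56% more patients as r goes from 0.3 to 0.6. For the mean of two or three visits it is 13–14% at r = 0.3 and 45–52% at r = 0.5. These figures rest on assumed values of r, an assumed correlation of 0.6 between visits, and equal SDs. The gain for pain is uncertain and may be smaller. That STAI-S is collected at T0 is read from its role as the baseline covariate, since the schedule figure is not available.

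**What to change.** In Data Analysis, extend the sentence on the T2 to Tx mixed models: the state anxiety model includes the T0 STAI-S score, and the pain model the T0 NRS pain score, as a fixed covariate. A T0-by-time term is optional.

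Use T0 and not T1. T1 is measured after randomization, and T1 state anxiety is itself the primary outcome. The PONV model needs no change on this account.

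The cost is one line of wording and one degree of freedom per model for the covariate itself; the optional interaction would use more. No new data are needed. Recruitment is still under way, so the change can be fixed before any results are seen and would not look data-driven.
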